#### Participants

Ten wheelchair-dependent boys with a DNA-established diagnosis of DMD will be recruited in the same way as the participants of study 1 (figure 5). Inclusion and exclusion criteria are described in table 3. Participants will receive written information and will be visited by the primary investigator at home for providing further information. Both parents and participants will need to give written informed consent. The study protocol was approved by the Medical Ethics Committee Arnhem-Nijmegen, the Netherlands.

**Figure 5 F5:**
[figure not shown]
**Progress study 2 Functional training with arm support**. This flowchart is a preliminary version. Final numbers may change depending on eligibility as recruitment is not yet complete.

**Table 3 T3:** Inclusion and exclusion criteria study 2

Inclusion criteria	Exclusion criteria
A DNA-established diagnosis of DMD	Other disabling diseases influencing mobility
Boys who have been wheelchair-dependent for a few years (approximately 2-5 years after they stopped walking)	Boys who are able to stand
	Boys >20 years old
Boys who have problems with reaching and lifting movements with their arms, and: -are unable to touch the top of their head (at least with one hand) -are still able to use their hands for some daily activities	Boys who already use an arm support

#### Intervention

The six-months physical training consists of 1) a computer-assisted training and 2) a functional training of the non-dominant arm and hand (i.e. the hand one does not use for writing) with a mechanical or an electrical arm support (Dynamic Arm Support Top/Help, Focal, Tilburg, the Netherlands) (figure 6). Boys who are unable to touch their nose with a mechanical arm support (due to insufficient muscle strength) will receive an electrical arm support. The arm support transposes shoulder movements into movements of the forearm and hand, which increases functional abilities and joint range of motion in boys with DMD. During the first baseline measurement (T0), boys will try to fit the arm support under supervision of an experienced representative of Focal (the manufacturer of the TOP arm support) and the primary investigator. Training of the non-dominant arm is additional to any regular therapy. All co-interventions will be registered.

##### Computer-assisted training

Boys play "Furballhunt" (developed by Roessingh Research and Development B.V. ([name]), Enschede, the Netherlands) to practice targeted forward and sideward reaching movements (ipsi- and contra-lateral) as well as lifting movements during five days per week. Furballhunt is a computer game that was originally developed to improve arm function in children with cerebral palsy using a virtual reality environment. Furballhunt is based on motion capture technology and uses a webcam (in this study: Logitech QuickCam E3500) to detect gross shoulder and elbow movements. Birds ("Furballs") fly from their bird-house to a tree branch while the boy holds his hand in front of his navel. Boys have to touch the Furball when it sits down on a tree branch. The faster boys chase away Furballs, the higher their score. A virtual reality computer game is considered to be a motivational tool for training in children[39].

Boys play five games of Furballhunt (30 Furballs per game, 30 sec of rest between games) per day at home. The number of tree branches (3), game speed (5/10), the number of Furballs (30) and the sequence of games are standardized. Training intensity is low to moderate, which means that boys are allowed to perceive their exertion as 'getting a little tired' or 'getting more tired' as assessed with the OMNI Scale[27]. Intensity is adjusted to the physical abilities of the boy by varying the position of the tree branches, which represent the targets to move to. Boys are instructed to move their arm over the full range of motion, which may cause a feeling of stretch but not pain.

Boys report their training frequency in a diary and complete an overstrain questionnaire once every two weeks. Parents and their boys are informed by telephone when compliance is inadequate or when other problems (such as signs of overstrain: see adverse events) are identified. Boys are encouraged to resume the training and to adjust the training intensity, when appropriate. The date, training time and reaction times are saved on the computer, so that compliance and performance can be checked afterwards by the primary investigator.

##### Functional training

Boys should eat at least one meal with the arm support twice every week. In addition, they are instructed "to use the arm support as much as possible every day". Boys keep a written record of all activities they perform with the arm support in a three-day diary once every two weeks (two weekdays, one weekend day).

#### Study outcomes

Study outcomes include measurements at the levels of body functions and structures, activities and participation of the ICF[29]. Environmental characteristics (school type and home status) are assessed at baseline. Demographic variables (age, weight, arm span), the use of medication (such as corticosteroids) and any co-interventions are registered during each session.

After a two-month period for baseline measurements (T0: at baseline; T1: after 4 weeks; T2: after eight weeks) to obtain information about the stability of the course of DMD, training with the arm support takes place for six months. Assessments take place after 12 weeks (T3) and 24 weeks (T4) training. Finally, one extra measurement will be done after 12 more weeks (T5) to evaluate to what extent the possible effects of training have lasted. Data is collected by the primary investigator (MJ) at the department of Rehabilitation of the Radboud University Nijmegen Medical Centre (T2, T4), but also at home (T0, T1, T3, T5) to reduce the practical burden on the participants. (figure 7).

**Figure 6 F6:**
[figure not shown]
**Dynamic arm support Top/Help**. Focal Meditech BV, Tilburg, the Netherlands (www.focalmeditech.nl)

**Figure 7 F7:**

**Measurements study 2**. BP (Baseline period), IP (Intervention period), FU (Follow-up)

##### Primary outcome

Action Research Arm Test (ARAT)

As no suitable measure of arm motor function has been validated for children with NMD, the functional abilities of the upper extremity (reaching, lifting and manipulating) are assessed bilaterally with the Action Research Arm Test (ARAT)[40]. The ARAT is a standardized tool for the assessment of arm motor function and capacity (both distally and proximally) and consists of 19 items in four dimensions: grasp, grip, pinch and gross movements. The ARAT has shown to be reliable[40,41], valid[40-42] and suitable to detect changes over time[42] in stroke patients. The ARAT is performed and scored following standardized procedures as described by Yazbatiran[41]. The non-dominant arm is assessed both with and without arm support.

##### Secondary outcomes

Table 2 shows an overview of the secondary study outcomes and their psychometric properties. Both the dominant and non-dominant arms are assessed. The non-dominant arm is assessed both with and without arm support.

#### Adverse events

All adverse events will be recorded. The study will be terminated prematurely for an individual participant when training is excessive and remains excessive after a reduction of the training intensity. Signs for overstrain are: excessive muscle pain during the training, prolonged post-exercise muscle pain, a severely uncomfortable feeling during or after the training and extreme (muscle) fatigue (OMNI scale > 6).

#### Sample size

This is a first explorative study that will give an indication of the effect of functional training with arm support on the functional abilities of the upper extremity in boys with DMD. In this perspective, no realistic power calculation can be made. By using a design with multiple measurements at baseline we anticipate to find statistically significant effects of the proposed therapeutic intervention in ten boys with DMD.

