	Upper limb function	Action Research Arm Test[40,41] ▪	Excellent intra-rater, inter-rater and test-retest reliability in stroke patients[40,41] Highly correlated with the Fugl-Meyer score^47 ^and Functional Independence Measure^48 ^in stroke patients Suitable to detect changes over time in stroke patients[42]	All

	Functional abilities (grading)	Vignos* and Brooke Scale*▪ [56]	Good inter-rater and intra-rater reliability[57,57] and correlated with timed tests[46,68,69] in DMD	All

	Functional mobility	Functional Mobility Scale[70] *	A clinically feasible, valid and reliable tool in CP[70,71]	All

	Functional abilities (timed tests)	Timed and graded functional tests (and total GSGC score) [72]: walk 10 meters, climb 3 stairs, rise from the floor and rise from a chair*	Good to excellent intra- and inter-rater reliability in DMD[57,73] Sensitive to change in DMD: a small reduction in muscle force was accompanied by a large increase in time it takes to complete functional tests[74]	All (gait, stairs and chair only in the hospital)

	Finger dexterity	Nine-hole Peg Test[75] *▪	Moderately high test-retest reliability, high inter-rater agreement and adequate concurrent validity in school-age children[76]	All

	Hand function	Jebsen-Taylor Hand Function Test[77] ▪	Good test-retest reliability in DMD[58] Strongly correlated with muscle strength of the wrist extensors[58], radial deviation range of motion[58] and the Brooke scale[46] in DMD	T2, T4, T5

	Functional status	PEDI[78,79] (selfcare*▪ and mobility*)	Good inter-rater and test-retest reliability[80], content validity[79] and discriminative validity[81] in children with various diagnosis Feasible for evaluative purposes in CP[81,82]	T0, T2, T4, T6/T7*

	Perceived manual abilities	Abilhand[83] ▪ Abilhand-kids[84] *	The Rasch-derived Abilhand is moderately related to grip and key pinch strength, has good test-retest reliability and may be sensitive to change in stroke patients[85] The Abilhand-kids has good test-retest reliability and a higher independence in gross motor function is associated with a higher manual ability in CP[84]	T0, T2, T4, T6/T7*

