	Quality of upper-limb motor function	Melbourne Assessment of Unilateral Upper Limb Function[86] (item 1,2,3,10,11 and16) extended with an upper limb motion analysis (Vicon Motion Systems) with 8 cameras▪	The Melbourne Assessment has moderate to high intra- and inter-rater reliability[87] and excellent construct validity in CP[88] A motion capture analysis system can measure task performance with an upper-limb orthosis[45], but soft tissue artefacts may negatively influence accuracy[49]	T2, T4

	Incidence and fear of falls	Semi-structured interview*		All

**Participation**	HRQoL	KIDSCREEN-52[89](child- and parental questionnaire)*▪	Acceptable levels of reliability and validity in children and adolescents[90] Children's most important in their lives generally map well to the items in KIDSCREEN[91]	T0, T2, T4, T6/T7*

**Demographic variables**	Weight and height	Body weight (kg)*▪, standing height* (cm) and arm-span*▪ (cm)		T0*, T2, T4, Y6/T7*

**Co-factors**	Co-interventions	Semi-structured interview*▪		All

	Physical activity	Semi-structured interview (according to the PAQ-C[92] and the 60-min MVPA measure[93])*▪		All

**Symbols:* **= study 1 'Dynamic leg and arm training', ▪ = study 2 'Functional training with arm support'

**Abbreviations**: DMD: Duchenne Muscular Dystrophy; PROM: Passive Range of Motion; ext: extension; dfl: dorsal flexion; abd: abduction; dev: deviation; MRC: Medical Research Council Scale; RF: m. Rectus Femoris; TA: m. Tibialis Anterior; BB: m. Biceps Brachii; FF: forearm flexors; NMD: Neuromuscular Disease; GSGC: Gait, Stairs, Gowers, Chair; PEDI: Pediatric Evaluation of Disability Inventory; CP: cerebral palsy; HRQoL: Health-Related Quality of Life; PAQ-C Physical Activity Questionnaire for older children; MVPA: Moderate-to-Vigorous Physical Activity

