### Study 2 Functional training with arm support

#### Design

Study 2 has an observational one-group design using repeated measurements, because we anticipate that it will not be possible to recruit a sufficient number of boys for an RCT in the Netherlands. This problem is related to the fact that boys with DMD who have been confined to a wheelchair already for several years often experience many barriers, such as a lack of time due to therapy obligations and homework. It is also virtually impossible for them to do without their electric wheelchair for a couple of days to build up the required arm support for this study. In addition, the number of boys at this stage in the course of DMD is low (i.e. an estimated 120 boys in the Netherlands) and, it is expected that some of these boys already use an arm support, which is an exclusion criteria for participation.

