#### Analysis

A one-way analysis of variance (ANOVA) of time will be used to examine the effects of functional arm training with arm support on the primary outcome (ARAT). Secondary outcomes will be treated similarly or by non-parametric analyses dependent on the type of outcome (interval or ordinal). Data will be analyzed with SPSS version 16.0 and an alpha level of 0.05 will be used to decide on statistical significance.

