### Study outcomes

In this study, reliable functional scales are used, such as the MFM, as well as timed tests that have clinically meaningful endpoints[47] and that are sufficiently sensitive to detect therapy related gains[48]. Indeed, outcome measures should be reliable and sensitive to allow for an adequate power in trials with a relatively small sample size. As no suitable ergometry test or arm motor function test is available for (non-ambulant) boys with NMD, a Six-Minute Bicycle test and the ARAT have been selected as primary outcomes. Pilot studies showed that the applied Six-Minute Bicycle test was feasible for both ambulant and recently wheelchair-dependent boys with DMD. The ARAT proved to be useful in a wheelchair-dependent boy with DMD as well (unpublished data). In addition, we used an upper extremity protocol to quantitatively measure arm motor function[49] with an eight camera motion analysis system (Vicon Motion Systems, Ltd, Oxford, UK). It has been shown that such a system can accurately measure task performance with an upper-limb orthosis[45]. Arm motor function has never been measured quantitatively before in boys with DMD, which may be of value because of its continuous properties and presumably greater sensitivity to change[50].

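### In uncontrolled Study 2, the Jebsen-Taylor test and the Melbourne/motion analysis have one pre-training value each, so the planned ANOVA of time confounds training with practice and disease course for these two secondary outcomes

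*Protocol article*

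**What the plan says.** All places are in the Protocol article, Study 2, unless noted.

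- **Design:** "Study 2 has an observational one-group design using repeated measurements".
- **Study outcomes:** T0, T1 and T2 fall at weeks 0, 4 and 8, before training, and serve "to obtain information about the stability of the course of DMD". T3 and T4 follow after 12 and 24 weeks of training, and T5 comes 12 weeks later to see how far any effect lasts. T2 and T4 are hospital visits; T0, T1, T3 and T5 are home visits.
- **Sample size:** "no realistic power calculation can be made", followed by "By using a design with multiple measurements at baseline we anticipate to find statistically significant effects of the proposed therapeutic intervention in ten boys".
- **Table 2:** the Jebsen-Taylor Hand Function Test is marked for Study 2 only, at T2, T4 and T5. The "Melbourne Assessment of Unilateral Upper Limb Function[86] (item 1,2,3,10,11 and16) extended with an upper limb motion analysis" is also marked for Study 2 only, at T2 and T4.
- **Secondary outcomes:** both arms are assessed, the non-dominant (trained) arm with and without the support.
- **Analysis:** a one-way ANOVA of time for the ARAT, at alpha 0.05. "Secondary outcomes will be treated similarly or by non-parametric analyses dependent on the type of outcome (interval or ordinal"). No contrast between arms is stated.
- **Discussion, Study outcomes:** quantitative motion analysis is said to be something "which may be of value because of its continuous properties and presumably greater sensitivity to change[50"].

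**The concern.** Without a control group, the repeated baseline is the only planned way to see what a boy's score does before training starts. It shows whether scores are stable, falling with the disease, or rising because the test is becoming familiar. The Jebsen-Taylor test and the motion analysis are first scheduled at T2, the last visit before training, so nothing about their untrained course is observed. The Analysis section still tests them for change over time.

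Two influences other than training can move such a score between T2 and T4. Practice between a first and second attempt would look like benefit. Natural decline in a progressive disease would hide a benefit or look like harm. Both directions matter, because the Background asks whether training helps and also whether it does no harm. The visit schedule is fixed in Table 2, and a T0 or T1 value that was never collected cannot be supplied later by an analysis plan.

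**Working it through.** **The plan's own figure.** The ten boys come without an effect size, SD or power, so there is nothing to reproduce.

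**Step 1: pre-training values by outcome (Table 2, Study 2 markers).**
- Three (all visits): ARAT, goniometry, MRC strength, MFM D3, Brooke Scale, Nine-hole Peg Test.
- Two (T0, T2): PEDI self-care, Abilhand, KIDSCREEN-52.
- One (T2): Jebsen-Taylor and Melbourne/motion analysis. By its visit codes muscle ultrasound also has one, but it is shared with Study 1 and is not a task a boy can practise, so it is left out here.

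**Step 2: can training be told apart from a time trend?** Take training as starting at T2, so that T2, T4 and T5 fall at weeks 8, 32 and 44. For one boy let Y = a + b·week + e·(training effect present), with residual SD σ.
- *Motion analysis (T2, T4).* Y4 − Y2 = 24b + e. Two values cannot fix three unknowns (rank 2 of 3), so e and b are fully aliased.
- *Jebsen-Taylor (T2, T4, T5).* If a share λ of the effect remains at T5, then Y5 − Y2 = 36b + λe, and e·(1 − 2λ/3) = (Y4 − Y2) − (2/3)(Y5 − Y2). The SE of e is σ·√(1 + 1/9 + 4/9)/(1 − 2λ/3): 1.25σ at λ = 0 and 3.74σ at λ = 1. The answer needs λ, which T5 is there to find out. A practice gain from the first attempt stays mixed with e whatever λ is.

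**Step 3: illustration of size.** With two time points, a within-boy ANOVA of time is the paired t-test. Inputs: n = 10, df = 9, alpha 0.05 (two-sided assumed; the document does not say), no training effect, and a non-training change of d SDs of the T2-T4 difference. Every d is an assumption. The noncentrality is d·√10 and the critical value is 2.262.

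| d | noncentrality | P(significant) |
|---|---|---|
| 0 | 0 | 5% |
| 0.25 | 0.79 | 11% |
| 0.5 | 1.58 | 29% |
| 0.75 | 2.37 | 56% |
| 1.0 | 3.16 | 80% |

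For the Jebsen-Taylor test this describes the T2-T4 contrast; an ANOVA over all three times would give somewhat different figures.

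**Step 4: what earlier values would add.** With T0, T1, T2 and T4, e is Y4 minus the baseline line carried forward to week 32. Its variance is σ²·[1 + 1/3 + (32 − 4)²/32] = 25.83σ², so the SE is 5.08σ per boy, or 5.08/√10 = 1.61σ for the mean of ten boys. With T0, T2 and T4 the SE is 5.10σ per boy. The effect becomes identifiable under a linear trend, but imprecisely, because 8 weeks are extrapolated over 24.

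**Step 5: what the other arm would add.** If practice and disease course move both arms equally, they cancel in D = (Y4 − Y2, trained) − (Y4 − Y2, untrained). With equal variances, Var(D) is 2(1 − ρ) times that of one arm's change, where ρ is the correlation between the two arms' changes. The documents do not give ρ. D is no noisier than the single-arm change when ρ is at least 0.5.

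**The case against.** The best defence is that these are two of many secondary outcomes in a study that calls itself explorative. The Design section explains why a control group was not thought feasible, and hospital-only equipment may explain the motion-analysis schedule. Much of this stands, and it rules out several stronger readings.

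- A reader might infer that the Sample size sentence is untrue. It is not contradicted: the primary ARAT and several other arm measures do have three baselines.
- A reader might infer that decline would be claimed as a benefit. Decline works against a claim of benefit; only practice would produce a false one, and the document quantifies no practice effect.
- A reader might attribute the 11% to 80% to the missing baselines. A one-way test of time does not remove drift even with three baselines, so those figures are the cost of any uncontrolled time test. The Discussion regards progression as relatively slow, so the larger values of d have no support from disease course.
- A reader might take these two outcomes as the most informative in the study. The document makes only a tentative remark about motion analysis, and none of that kind about the Jebsen-Taylor test.
- Nor is separation impossible in principle, since the untrained arm is also assessed.

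Two things are not answered. The stated analysis is a one-way test of time that makes no use of the other arm. And the location of visits does not explain the Jebsen-Taylor schedule, since that test is already planned at T5, a home visit like T0 and T1.

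**Conclusion.** The point holds, limited to two secondary outcomes. Followed as written, the plan would test the T2-T4 change in the Jebsen-Taylor test and the Melbourne/motion analysis at alpha 0.05 with nothing to set it against, so neither a gain nor a loss could be credited to training. The aliasing follows directly from Table 2 and the Analysis section. The 11% to 29% is only illustrative: it assumes a non-training change of 0.25 to 0.5 SD, a two-sided paired test and ten complete pairs.

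A reader might go further and call the results uninterpretable, or doubt the primary analysis on this ground. The documents do not support that: the ARAT has its full baseline series, and data on the untrained arm are planned. This is a worthwhile and inexpensive improvement, not a flaw that undermines Study 2.

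**What to change.** 1. For both outcomes, replace the one-way ANOVA of time by the T2-T4 change of the trained non-dominant arm, tested without the support, minus that of the untrained dominant arm. Give it with a confidence interval. The Secondary outcomes section already plans these measurements, so the cost is a sentence in the Analysis section. Say openly that the dominant arm is an imperfect comparator: the Discussion notes that the two arms are used to different degrees, and practice or training may carry over between them.
2. Add the Jebsen-Taylor test at T0 and/or T1, as a check on practice and short-term stability and not as a precise slope correction (Step 4). No new visits are needed. Testing each arm unsupported means two extra administrations per boy at one visit or four at two. Including the supported condition would make it three or six, which matters because the home visits were chosen to limit burden.
3. Otherwise, report the T2-T4 changes of both outcomes with confidence intervals as descriptive, and do not claim a training effect from them.

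The price is a modest added test burden per boy and a weaker claim for two secondary outcomes.

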#### Analysis

A one-way analysis of variance (ANOVA) of time will be used to examine the effects of functional arm training with arm support on the primary outcome (ARAT). Secondary outcomes will be treated similarly or by non-parametric analyses dependent on the type of outcome (interval or ordinal). Data will be analyzed with SPSS version 16.0 and an alpha level of 0.05 will be used to decide on statistical significance.

